### Eligibility

All adults aged 60 and older living in the study area who will be contacted by the study team can participate in the study. Older adults residing in long-stay institutions for the elderly and those who are bedridden will be excluded from our study as the focus of this research is the follow-up of IC until the development of one or more outcomes: severe dependence, fall, hospitalization, or death as a function of IC. It will also be important to ensure through an initial in-house geriatric assessment that participants at baseline do not have significant loss of independence in the activities of daily living (ADL and IADL scores >0) (Katz and Akpom, 1976; Lawton and Brody, 1969) and cognitive ability (Clinical Dementia Rating (CDR) > zero) (Morris, 1994).

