**FIGURE 1 F1:**
[figure not shown]
Proposed study design.

In a period of 6 months, we expect that a team of trained interviewers will contact all potential cohort participants. Based on information from a recent study on the association of IC with the outcome incidence rates of functional dependence, falls, and death (Prince et al., 2021), we developed sample size estimates for comparing two proportions that represent the rates of outcomes in the groups that are exposed (low IC) and unexposed (medium or high IC) (see Tables 1, 2). Calculations considered various effect sizes (relative risk) and incidence or mortality rates. In estimating the sample size needed for this cohort study, this study considered the incidence of the expected outcome in the unexposed cohort (high IC), the risk assumed in the exposed group relative to the risk of the unexposed group (RR), a specific level of confidence (1-α = 0.95; where α = type I error rate), and a specific value of the desired sample power (1-β = 0.80; where β = type II error rate) for the detection of significant differences between the two cohorts. The outcome incidence rate in the cohort was used as a proxy for the expected outcome incidence rate in the unexposed group (high IC). The summary tables (Tables 1, 2 below) provide sample sizes for extremes of the assumed incidence and mortality rate values and the respective relative risks based on the confidence intervals of these measures. A total sample size of approximately 5,500 individuals (assuming 2,750 per group) will be sufficiently robust to maintain the desired power under most diverse scenarios and varying parameters, even if the dropout rate reaches approximately equal to 15% in the two cohorts. The exception will be with very small estimates of the relative risk of death (RR ≤ 1.3).

**TABLE 1 T1:** Sample sizes for specific values of functional loss (FL), incidence, and relative risk for intrinsic capacity (IC) and FL.

	Average risk ratio	Low risk ratio	High risk ratio
Risk ratios (RR)	1.91	1.7	3.0
Incidence rate among the unexposed group	0.0495	0.04925	0.04925
Confidence level (1-α)	0.95	0.95	0.95
Power (1-β)	0.8	0.8	0.8
Study type	Cohort	Cohort	Cohort
Sample per group (n_i_)	514	816	138
Total sample (n_1_+n_2_)	1,028	1,632	276

**TABLE 2 T2:** Sample sizes for specific values of total mortality (TM) and relative risk for IC and TM.

	Average risk ratio	Low risk ratio	High risk ratio
Risk ratios (RR)	1.66	1.3	2.0

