Mortality rate among unexposed	0.04826	0.04826	0.04826
Confidence level (1-α)	0.95	0.95	0.95
Power (1-β)	0.8	0.8	0.8
Study type	Cohort	Cohort	Cohort
Sample per group (n_i_)	926	3,922	432
Total sample (n_1_+n_2_)	1,852	7,844	864

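### The sample-size tables vary only the relative risk, not the incidence or mortality rate as the text says, and the stated exception (death, RR ≤ 1.3) is too narrow at the plan's own rate

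*Protocol article*

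**What the plan says.** All of this is in the protocol article, in the section on study sample size and power, with Tables 1 and 2.

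- On method, the text says: "Calculations considered various effect sizes (relative risk) and incidence or mortality rates". The tables are then said to "provide sample sizes for extremes of the assumed incidence and mortality rate values and the respective relative risks based on the confidence intervals".
- Table 1 (functional loss) has columns for an average, a low and a high risk ratio: 1.91, 1.7 and 3.0. Its rate row reads: "Incidence rate among the unexposed group 0.0495 0.04925 0.04925". The sizes per group are 514, 816 and 138.
- Table 2 (mortality) has RRs of 1.66, 1.3 and 2.0. Its rate row reads: "Mortality rate among unexposed 0.04826 0.04826 0.04826". The sizes per group are 926, 3,922 and 432.
- Confidence is 0.95 and power 0.80 throughout.
- The conclusion is that about 5,500 people, taken as 2,750 per group, "will be sufficiently robust to maintain the desired power under most diverse scenarios and varying parameters", even with about 15% dropout in both groups. The one exception named is a relative risk of death of 1.3 or less.
- The unexposed rate is a proxy: the incidence in a whole cohort stands in for that of the high-IC group.

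**The concern.** The size needed to compare two proportions depends on the baseline risk and the relative risk together. The text says both were taken to their extremes, but the tables move only one of them. A reader who relies on the text will believe that a low event rate has been tried and that the sample survived it.

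A lower rate than printed is possible. If RR is above 1, a whole-cohort rate overstates the rate in the lower-risk unexposed group. The Eligibility section also leaves out people in long-stay institutions, those who are bedridden and those with significant loss of independence. These points give a direction, not a figure.

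Separately, the exception is set at the lowest RR that happened to be tabulated. Nothing in the tables shows that power reaches 80% just above it.

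**Working it through.** **Inputs from the protocol article.** Rates and RRs as printed in Tables 1 and 2; α = 0.05; power 0.80; equal groups of 2,750; dropout 15%, so 2,750 × 0.85 = 2,337 per group. Whether α is one- or two-sided is not stated. Two-sided reproduces the tables and one-sided does not.

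**Step 1: reproduce the tables.** With p1 = RR × p0 and unpooled variance,

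n = (1.960 + 0.842)² × [p0(1 − p0) + p1(1 − p1)] / (p1 − p0)², where (1.960 + 0.842)² = 7.849.

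Example, Table 2 low RR: p0 = 0.04826, p1 = 1.3 × 0.04826 = 0.06274, so n = 7.849 × (0.04593 + 0.05880) / 0.01448² = 3,922.

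| Column | Printed rate | RR | Printed n | n at printed rate | n at rate 0.05 |
|---|---|---|---|---|---|
| Table 1 average | 0.0495 | 1.91 | 514 | 514 | 508 |
| Table 1 low | 0.04925 | 1.7 | 816 | 816 | 803 |
| Table 1 high | 0.04925 | 3.0 | 138 | 140 | 138 |
| Table 2 average | 0.04826 | 1.66 | 926 | 926 | 891 |
| Table 2 low | 0.04826 | 1.3 | 3,922 | 3,922 | 3,778 |
| Table 2 high | 0.04826 | 2.0 | 432 | 449 | 432 |

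Four entries are exact. The two high-RR entries do not follow from their printed rates, but both are exact at 0.05.

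**Step 2: how far the rate varies.** In Table 2 it does not vary. In Table 1 the spread is 0.0495 − 0.04925 = 0.00025, about 0.5% of the rate. Even if the high-RR columns used 0.05, all rates lie between 0.048 and 0.050. None is an extreme.

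**Step 3: the exception, at the printed mortality rate.** Power for p0 = 0.04826 (usual pooled two-proportion test; the unpooled version agrees to the figures shown):

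| RR | 2,750 per group | 2,337 per group |
|---|---|---|
| 1.30 | 65% | 58% |
| 1.35 | 77% | 70% |
| 1.40 | 87% | 81% |

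Solving for 80% power gives RR = 1.36 without dropout and RR = 1.40 with it. RRs between 1.3 and about 1.4 therefore also fall short. This step uses no figure from outside the plan.

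**Step 4: sensitivity to the rate.** The documents give no range, so the 2% and 3% below are assumptions, on the tables' own risk scale. With 2,337 per group:

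| Unexposed risk | Smallest RR with 80% power |
|---|---|
| 4.826% (printed) | 1.40 |
| 3% (assumed) | 1.52 |
| 2% (assumed) | 1.66 |

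In the other direction, the lowest unexposed risk that keeps 80% power is 1.2% for functional loss at RR 1.91, 1.8% for functional loss at RR 1.7, and 2.0% for death at RR 1.66.

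**The case against.** The strongest reply is that the conclusion largely survives. At both average RRs, and at the low RR for functional loss, the sample tolerates rates well under half of those printed. The text claims only most scenarios and already names a small-RR exception for death. This stands: robustness to the rate is not shown, but it has not been shown to be false.

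A second reply concerns time. The tables give rates without a time unit, and follow-up lasts 3 years. If 0.04826 were annual (an assumption), the 3-year risk would be 1 − (1 − 0.04826)³ = 13.8%, and power at RR 1.3 after dropout would be about 97%. This also stands as a caution. However, the plan's own sizes and its own exception put 0.04826 directly into the formula as the risk, and on that footing the exception is too narrow. Stating the time base is part of the repair.

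Third, excluding people who are already dependent need not lower the incidence of new dependence, because incidence is counted among those free of it. So a lower rate is possible, not established.

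A reader might also infer that a Table 1 RR is wrong. Limits of one ratio interval are usually symmetric on the log scale, yet √(1.7 × 3.0) = 2.26, against 1.91. The documents do not support that inference. They refer to confidence intervals in the plural, never say that 1.7 and 3.0 bound a single interval around 1.91, and the source is not at hand. All that follows is that the values should be checked.

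**Conclusion.** The concern holds as an inconsistency between text and tables, together with a power statement that is wrong as written. The tables do not cover extremes of the rates, so the general robustness claim is unsupported with respect to the rate. On the plan's own inputs, the death exception should begin near RR 1.40 after dropout, or 1.36 without it, and not at 1.3.

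This rests on a two-sided 0.05 test, equal groups, 15% dropout in each group, and the printed rate read as the risk over follow-up. Results at 2% and 3% rest on assumed rates.

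It would go too far to conclude that 5,500 is inadequate, since the average-RR scenarios keep a wide margin. The entries 138 and 432 are minor discrepancies (140 and 449 at the printed rates) and do not affect the total.

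**What to change.** 1. Add columns at the lower and upper limits of each source rate, crossed with the RRs, and state the time base of the rates. Alternatively, delete the words that claim extremes of the rates.
2. Replace the robustness sentence and the RR ≤ 1.3 exception by the smallest RR detectable with 80% power after 15% dropout at each rate. At the printed mortality rate, read as a risk over follow-up, this is about 1.40.
3. Recompute the two high-RR entries, or correct the rates printed above them, so that each size follows from its own column.
4. Check the Table 1 RRs against the source, and say which interval or intervals they come from.

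The cost is a few table columns and a rewritten sentence or two. No participants, visits or analyses are added. The stated power becomes somewhat less favourable for small mortality effects.

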### Instruments and measures

To assess IC and its relationship with FA in older adults, a range of clinical and behavioral factors will be investigated through comprehensive geriatric and gerontological interviews and laboratory tests (Figure 2). In summary, the main variables of this research are as follows:

**FIGURE 2 F2:**
[figure not shown]
Intrinsic capacity: its domains, subdomains, and related health outcomes.

## Dependent variables

• Need for help in ADL (Katz and Akpom, 1976) and IADL (Lawton and Brody, 1969).• Falls in the last year.• Hospitalizations in the last year.• Deaths.

Explanatory variables: IC domains and subdomain measures.

The IC subdomain measures, their levels, cut off points for a binary classification, and references are presented in Table 3.

**TABLE 3 T3:** Intrinsic capacity domains and subdomains measures with classification cut-offs.

Domain	Subdomain	Classification (binary: 0 or 1)	References
Vitality	Number of chronic morbidities	<2 = 0 | ≥ 2 = 1	Charlson et al. (2022) and Charlson et al. (1987); Kim et al. (2021)
	Number of medications taken daily	0–4 = 0 | 5+ = 1	Golchin et al. (2015)
	Handgrip strength	Men:<=36.2 kg = 0 | > 36.2 kg = 1; Women:<=23.0 kg = 0 | > 23.0 kg = 1	Amaral et al. (2019), Alqahtani et al. (2019)
	Body mass index	≤ 25 = 0 | > 25 = 1	Kiskaç (2022), Krzyminska-Siemaszko et al. (2014)
	Biomarkers of metabolism and inflammation	NL = 0 | high = 1	Liu et al. (2017), Bautmans et al. (2022), Bohannon (2019)
	Pain numerical rating scale (NRS)	≤ 6 = 0 | > 6 = 1	Devin and McGirt (2015), Atisook et al. (2021)
Mobility	Tandem stance	Tandem stance for>=10 s = 0 | tandem stance for <10 sec= 1	Joo et al. (2021)
	Gait (timed up and go)	<6 min = 0 | ≥ 6 = 1	Herman et al. (2011); Alexandre et al. (2012)
Sensory	Community screening for visual impairment	Good = 0 | impaired = 1	Clarke et al. (2018)
	Hearing screening in older adults	Good = 0 | impaired = 1	https://hign.org/consultgeri/try-this-series/hearing
Cognitive	Memory (MOCA)	≥ 25 = 0 | < 25 = 1	Nasreddinne et al. (2005)
	Cognitive abilities (CDR)	0 = 0 | ≥ 0,5 = 1	Morris (1994)
Psychological	Depressive symptoms (GDS)	<5 = 0 | ≥ 5 = 1	Almeida and Almeida (1999), Yesavage et al. (1983)
	Sleep quality	good = 0 | bad = 1	Smyth (2013)

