### Explanatory variables: IC composite index (ICI)

An IC composite score or index (IC index or ICI) will first be created, as suggested by Gutiérrez-Robledo et al. (2019). This score aims to express a summary measure of impairments for an older adult. Initially, each continuous or ordinal subdomain measure will be dichotomized based on acceptable cut-off points to create a binary variable of 0 or 1 (see Table 3 for cutoff points across all subdomain measures). Within a domain, the values of these recoded subdomain measures will be summed up to create a “subdomain score.” The subdomain scores will range from 0 to 2 for the four subdomains with only two measures and from 0 to 6 for the subdomain with six measures (i.e., vitality). Then, each domain of the five IC components will be subdivided into three categories based on the sum of the scores of its subdomains, with the following numerical score: no impairment = 0, mild impairment = 1, and severe impairment = 2. For example, the four domains with only two subdomain measures (e.g., cognitive with subdomain measures memory and cognitive) will be coded 0 if their subdomain score (sum of their subdomain measure) is 0, 1 if the subdomain score value is 1, and 2 if the subdomain score value is 2. The domain with six subdomain measures, vitality (subdomains comorbidity, medication, biomarkers, pain, strength, and nutrition), will be coded 0 if its subdomain score is 0, 1 if the subdomain score is 2–4, and 2 if the subdomain score is 5–6. Scores for each of the five domains will be summed up to produce a composite IC index ranging from 0 (best possible ICI) to 14 (worst possible ICI).

Subsequently, this baseline ICI will be classified in four ways. First, using the terciles of ICI (TIC), ICI values less than or equal to the first tercile (Q1) will be classified as low TIC; ICI values between Q1 and the third tercile (Q3), including Q3, will be classified as medium TIC; and ICI values above Q3 will be classified as high TIC. This analysis model is explicitly shown in Figure 1.

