### Generation of weighted IC score (WIC)

To build the weighted IC score (WIC), first, associations between subdomains of IC domains (sensory, mobility, vitality, cognitive, and psychological) and IADL loss will be evaluated by IADL models in a two-stage logistic regression (Meng et al., 2022). For this purpose, IC subdomains will be dichotomized, such as body mass index (BMI) (overweight–obese v. normal–underweight) and handgrip strength (normal–strong v. weak), both of which are subdomains of the vitality domain (Chen et al., 2020). The first stage of modeling requires bivariate analysis between each IC subdomain and IADLs to identify candidate subdomains to enter the multivariate logistic model (Meng et al., 2022). For this, the variable in the model whose *p-*value for the statistical test of association (chi-square) with IADL is less than or equal to α = 0.25 will enter the multivariate logistic regression model with adjustment for the sociodemographic, comorbidity, behavioral, and clinical factors. An exception will be variables selected *a priori* since they are clinically fundamental, such as BMI from the vitality domain.

In the multivariate logistic regression model, subdomains whose *p-*values are less than or equal to α = 0.05 (statistically significant) will be used to generate WIC as follows. For the regression coefficient in the multivariate model that reaches statistical significance (*p ≤* 0.05), its component will be transformed into a subdomain score by dividing the coefficient by the smallest regression coefficient in the model after rounding the absolute value of the coefficient to the nearest integer value. Regression coefficients that are not statistically significant in the adjusted model will have a value of one (1) point. A summary WIC will be obtained by adding points from all regression components. The subdomain terms will enter the multivariate regression model such that the higher the WIC score, the better the IC.

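### Table 3 scores strong handgrip as the impairment and weak grip as normal, so one vitality item enters the intrinsic capacity index with the wrong sign; the Timed Up and Go cut-off also lacks a consistent unit

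*Protocol article*

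**What the plan says.** Table 3 (section Dependent variables) turns each subdomain measure into a 0/1 item. For handgrip it gives "Men:<=36.2 kg = 0 | > 36.2 kg = 1" and "Women:<=23.0 kg = 0 | > 23.0 kg = 1".

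The section on the IC composite index fixes the direction in three places:

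- The purpose: "This score aims to express a summary measure of impairments for an older adult".
- The domain categories: "no impairment = 0, mild impairment = 1, and severe impairment = 2".
- The total: a "composite IC index ranging from 0 (best possible ICI) to 14 (worst possible ICI").

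Vitality has six items. A sum of 0 is coded 0, a sum of 2 to 4 is coded 1, and a sum of 5 or 6 is coded 2. A sum of 1 is given no category.

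The mobility domain has two items. Tandem stance reads "Tandem stance for>=10 s = 0 | tandem stance for <10 sec= 1". Timed Up and Go is coded 0 below 6 minutes and 1 at 6 or more, with no unit on the second half.

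The Eligibility section says participants should not, at baseline, have significant loss of "cognitive ability (Clinical Dementia Rating (CDR) > zero"). Table 3 scores a CDR of 0.5 or more as 1.

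**The concern.** In a sum of impairments, every item must take the value 1 in its impaired state. The rows of Table 3 with an explicit direction do so: tandem stance, vision, hearing, MoCA, CDR, depressive symptoms, sleep, pain, morbidities and medications. Handgrip does the reverse for both sexes.

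The index is the study's central exposure and, through ∆IC, also an outcome. Coded as printed, stronger people gain an impairment point and weaker people lose one. A participant whose grip falls below the cut during follow-up loses an impairment point. That works against the first research question (whether IC declines over three years) and puts error into the exposure groups of the Cox models.

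The Timed Up and Go cell raises a different problem. Its unit is incomplete, and the unit that is printed sits oddly beside a mobility item timed in seconds.

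**Working it through.** **1. Direction of the handgrip item.**

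| Source | Meaning of 0 | Meaning of 1 |
|---|---|---|
| Index definition | no impairment | impairment |
| Tandem stance (Table 3) | held 10 s or longer | held less than 10 s |
| Handgrip, men (Table 3) | 36.2 kg or less | above 36.2 kg |
| Handgrip, women (Table 3) | 23.0 kg or less | above 23.0 kg |

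The two handgrip rows contradict the first row. The section on the weighted score names the categories as "handgrip strength (normal–strong v. weak"). That confirms which class is regarded as normal, but it assigns no codes, so the proof rests on Table 3 and the index definition.

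**2. Effect on the vitality score.** The stated range reproduces: six binary items give 0 to 6. Let k be the number of positive items among the other five. The vitality category is in brackets, and a dash marks the unassigned score of 1.

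| k | Strong, as written | Strong, swapped | Weak, as written | Weak, swapped |
|---|---|---|---|---|
| 0 | 1 (–) | 0 (0) | 0 (0) | 1 (–) |
| 1 | 2 (1) | 1 (–) | 1 (–) | 2 (1) |
| 2 | 3 (1) | 2 (1) | 2 (1) | 3 (1) |
| 3 | 4 (1) | 3 (1) | 3 (1) | 4 (1) |
| 4 | 5 (2) | 4 (1) | 4 (1) | 5 (2) |
| 5 | 6 (2) | 5 (2) | 5 (2) | 6 (2) |

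Every score is off by one in the wrong direction. At k = 4, mild and severe change places. A person with no impairment and strong grip scores 1 instead of 0. A person impaired on everything, with weak grip, scores 5 instead of 6.

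**3. Effect on change.** Take k = 4 at both visits and grip falling below the cut. As written, vitality moves from 5 (severe) to 4 (mild), so ICI falls by 1, an apparent improvement. With the codes swapped it moves from 4 to 5 and ICI rises by 1.

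**4. Share in the wrong vitality category.** Strong and weak participants change category at the same values of k, so the share does not depend on how many have weak grip. Assume the other five items are independent with common prevalence p.

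If a score of 1 is read as mild, the category is wrong at k = 0 and k = 4: share = (1−p)^5 + 5p^4(1−p).

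- p = 0.10: 0.5905 + 0.0005 = 0.591
- p = 0.30: 0.1681 + 0.0284 = 0.196
- p = 0.40: 0.0778 + 0.0768 = 0.155
- p = 0.50: 0.0313 + 0.1563 = 0.188

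If a score of 1 is read as no impairment, it is wrong at k = 1 and k = 4: share = 5p(1−p)^4 + 5p^4(1−p). At p = 0.30 this is 0.3602 + 0.0284 = 0.389.

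The prevalences are assumptions; the document gives none.

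**5. Timed Up and Go.** Two binary items give the stated mobility range of 0 to 2. If 6 means minutes and nobody reaches it, mobility runs 0 to 1, severe mobility impairment cannot occur, and the five-domain sum tops out at 4×2 + 1 = 9 instead of 5×2 = 10. If 6 was meant in another unit, the item behaves quite differently.

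**6. CDR.** Eligibility removes CDR above 0, so the item is 0 for everyone at baseline and can only stay or worsen.

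**The case against.** **Handgrip.** One could suspect a slip in reading the table from PDF. That is unlikely, because both halves of the coding agree for both sexes. One could also say the intended direction is obvious and a programmer would correct it. It may be obvious, but the table is the scoring rule, and following it gives the wrong sign. The weighted score (WIC) is less clearly affected: its weights come from regression using absolute coefficients, and its terms are to be entered so that higher means better. The sample-size tables do not depend on the coding.

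**Timed Up and Go.** A reader might infer that this item can never be positive. The document does not support so firm a statement. It neither describes the test nor gives usual times, and the upper half of the cell has no unit. What stands is that the cell is inconsistent. Read as minutes, the item would practically never be positive in a cohort that excludes bedridden people and those with significant ADL or IADL loss.

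**CDR.** A reader might infer that the item builds in spurious decline and must leave the change score. But a uniform start at CDR 0 follows from a deliberate eligibility rule, and a later CDR of 0.5 or more is decline in the construct being measured. Dropping it from ∆IC alone would also mean that ∆IC was no longer the difference of the defined index. What stands is narrower: the item does not discriminate at baseline and can move only one way.

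**Size.** A single figure of 20% misclassified would be arithmetically right at 30% prevalence but not robust. A highest attainable baseline index of 8 (2+1+2+1+2) requires both the minutes reading of Timed Up and Go and the CDR premise, so it is not relied on here.

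**Conclusion.** The handgrip coding is wrong as written and must be corrected; this follows from the document alone. Each participant's vitality score moves by one point the wrong way. The error passes into ICI, TIC and ∆IC, and into DIC where that is judged on domain scores. In the scenarios computed, the share in the wrong vitality category is about 15% to 59%. That range assumes five independent items of equal prevalence between 10% and 50%, and it depends on how a vitality score of 1, which the plan leaves unassigned, is read.

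The Timed Up and Go cell is defective in its unit and needs reconciling. Its consequence for the mobility domain is conditional on the minutes reading. The CDR item is a limitation worth showing, not an error.

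**What to change.** - **Handgrip (required):** in Table 3, code grip at or below the cut as 1 and above it as 0, for men and for women. This changes one table row. The article states that no data have been collected, so nothing has to be rescored.
- **Timed Up and Go (required):** check unit and cut-off against the references cited in that row and print the same unit on both sides. No cut-off is proposed here. The cost is one table cell.
- **CDR (optional):** keep ∆IC as defined and add a sensitivity analysis that shows it with and without the CDR item. The cost is one extra analysis; in the version without CDR, the cognitive domain rests on MoCA alone.
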